In existing studies, the utilization of LUS to assess NRDS often involves simplified adaptations from adult LUS systems. A unified standard for LUS assessment in neonates remains elusive (14, 15). Variations exist in the scoring locations and methods of LUS applied across different studies. Furthermore, a consensus on the threshold of LUS for PS application has yet to be established, hindering its widespread clinical application. Therefore, this study aimed to demonstrate, through a randomized controlled trial, that for very preterm infants (< 32 weeks GA) experiencing respiratory distress, determining PS application based on LUS combined with clinical indications can lead to more accurate NRDS diagnosis compared with traditional methods that rely on clinical indications and chest x-rays. Hence, this approach may facilitate the early and appropriate use of PS, within 3 h postnatally, thereby reducing mechanical ventilation duration, improving patient outcomes, lowering the incidence of BPD, and decreasing medical expenses. Furthermore, lung ultrasonography can partially substitute for chest x-rays in the diagnosis of early NRDS, significantly reducing early radiation exposure for patients.

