### Assessment points

2.6

The main assessment and recording of the infants’ indicators will occur at the following time points (Table 1).

**Table 1 T1:** Neonatal assessment chart.

Measure	Assessment point							
	Allocation within 1 h after birth	4–10 h after PS	24 h	3 days	7 days	14 days	28 days	36 weeks CA/discharge
LUS	×	×	×	×	×	×	×	×
Clinical index								
Silverman Anderson score	×	×	×	×	×	×	×	×
Respiratory support mode	×	×	×	×	×	×	×	×
Ventilator parameters	×	×	×	×	×	×	×	×
Medication use of PS	×		×					
Outcomes assessment								
NIV (hours)								×
IMV (hours)								×
Supplemental oxygen (days)								×
PS (%)								×
Early PS (%)								×
Birth to the application of 1st PS (min)								×
LOS								×
Costs associated with hospital care								×
Complications								
hsPDA (%)								×
BPD (%)								×
IVH (%)								×
NEC stage I or II (%)								×
ROP (%)								×

NIV, non-invasive ventilation; IMV, invasive mechanical ventilation; Early PS, pulmonary surfactant administered within 3 h after birth; LOS, length of stay; hsPDA, hemodynamically significant patent ductus arteriosus; IVH, intraventricular hemorrhages; BPD, bronchopulmonary dysplasia; NEC, necrotizing enterocolitis; ROP, retinopathy of prematurity.

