### Data collection and diagnoses

2.10

Patient demographic data mainly include: (1) GA, birth weight, singleton or multiple births, sex, prenatal steroid use, mode of delivery, presence of intrauterine distress, and maternal pregnancy complications; and (2) Apgar scores at 1 min, 5 min, and 10 min, as well as umbilical cord blood gas analysis.

Clinical information at each time point (at admission, 1 h after birth, 4–10 h after PS administration, 24 h, 72 h, 7 days, 14 days, 28 days, and before discharge or at 36 weeks CA) include (1) timing, dosage, and method of the initial PS administration; (2) SAS, respiratory machine mode, oxygen saturation index, and FiO_2_ levels at each time point; and (3) LUS at each time point. LUS will collect individual scores for each lung field as well as the total score.

Complications and outcomes: (1) Respiratory complications: this includes the occurrences of infectious pneumonia, pneumothorax, pulmonary hemorrhage, and BPD, along with their severity grading; (2) Cardiovascular complications: specifically, hemodynamically significant patent ductus arteriosus (hsPDA); (3) Other complications in premature infants: these encompass IVH, periventricular leukomalacia, NEC, late-onset sepsis, ROP, intrauterine growth restriction, and more; and (4) Length of hospital stay and associated costs.

BPD diagnosis will adhere to the 2018 National Institute of Child Health and Human Development (NICHD) classification. Diagnosis of hsPDA will rely on clinical signs and echocardiography (20). IVH and white matter injury will be diagnosed via cranial ultrasound, with IVH graded using the Papile classification (21). NEC staging will follow modified Bell criteria (22). ROP diagnosis and staging will be based on fundoscopic examinations conducted by ophthalmologists.

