### Sample size calculation

2.12

With the duration of mechanical ventilation as the primary outcome measure for both groups, we anticipate that patients in the conventional treatment group will require an average of 96 ± 12 h of respiratory support based on previous departmental data. It is expected that integrating ultrasound diagnosis will promptly improve respiratory function, reducing the mechanical ventilation duration to an average of 86 ± 12 h. To compare the difference in mechanical ventilation duration between the groups, a two-sample independent *t*-test will be employed, setting α at 0.05 and ensuring a power of 80%. With a 1:1 ratio between the groups, sample size estimation using PASS15 indicates that each group will require 24 patients, totaling 48 patients. Considering the potential risk of underestimating sample size due to low effect size and dropout rates, the actual sample size will be 60 patients (48 ÷ 80% = 60), with 30 patients in each group.

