### Statistical analysis

2.13

The demographic and clinical characteristics of both the ultrasound and control groups will be described using means and standard deviations, medians and ranges, or ratios and percentages. Statistical analyses will be conducted using SPSS 20.0 software. Normally distributed continuous data will be presented as means ± standard deviations, with inter-group comparisons assessed using independent two-sample *t*-tests. Non-normally distributed continuous data will be presented as M (Q1, Q3), with inter-group comparisons analyzed using the Mann-Whitney *U*-test. Categorical data will be expressed as counts (%), and inter-group comparisons will be evaluated using the *χ*^2^ test, continuity-corrected *χ*^2^ test, or Fisher's exact test. A *P*-value of less than 0.05 will be considered statistically significant.

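### The general rule in 2.13 would report skewed hospital cost only as medians with a rank test, which does not estimate the change in mean (hence total) expense

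*Protocol article*

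**What the plan says.** Cost appears in three places in the protocol article. The Background includes "lowering the incidence of BPD, and decreasing medical expenses" among the gains that may follow from ultrasound-guided surfactant. Table 1 in 2.6 has the row "Costs associated with hospital care" in its outcomes block, assessed at 36 weeks corrected age or discharge. Section 2.10 collects "Length of hospital stay and associated costs" for each infant. Section 2.9 does not list cost as a primary or secondary outcome.

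Section 2.13 gives one analysis rule for continuous variables. "Normally distributed continuous data will be presented as means ± standard deviations" and compared by a two-sample *t*-test. For the rest: "Non-normally distributed continuous data will be presented as M (Q1, Q3), with inter-group comparisons analyzed using the Mann-Whitney" *U*-test. "A *P*-value of less than 0.05 will be considered statistically significant". No variable is exempted.

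**The concern.** A statement that expenses fell is a statement about money spent. Total spending in an arm is its mean cost multiplied by its number of infants, so the matching comparison is between arithmetic means. The Mann-Whitney test asks which arm tends to have the higher value in a random pair, and the median ignores how expensive the costliest infants are.

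That skewed cost is likely is my assumption, but a mild one. Cost cannot be negative and follows length of stay, in infants below 32 weeks, some of whom will develop BPD, NEC or IVH. The 2.13 rule would then produce medians, quartiles and a P-value, and no estimate of the change in expense. If the two cost distributions also differ in shape, the rank comparison and the means may disagree in sign. At stake is one descriptive claim about cost. The primary outcome is untouched.

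**Working it through.** **The plan's own figure.** The only figure to reproduce is the sample size in 2.12, which concerns ventilation duration: the control group "will require an average of 96 ± 12 h of respiratory support", the ultrasound group 86 ± 12 h, "setting α at 0.05 and ensuring a power of 80" per cent. With a difference of 10 h and an SD of 12 h, the two-sided *t*-test calculation gives 23.6, so 24 per group (power 80.7%), and 48 ÷ 0.80 = 60. The figure reproduces and has no bearing on cost. The documents give no cost figure, so every cost below is an assumption in arbitrary units.

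**Step 1: can ranks and means disagree at 30 v 30?** Constructed example:
- Ultrasound: 24 infants evenly spaced from 60 to 85 (24 × 72.5 = 1740) and 6 evenly spaced from 250 to 400 (6 × 325 = 1950). Total 3690, mean 3690 ÷ 30 = 123, median 75.8.
- Control: 30 infants evenly spaced from 75 to 125. Total 3000, mean 100, median 100.
- Mann-Whitney U = 215 against a midpoint of 30 × 30 ÷ 2 = 450, two-sided p = 0.0005, in favour of ultrasound. Yet 3690 ÷ 3000 = 1.23, so its mean and total are 23% higher.

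**Step 2: what does a disagreement need?** Log-normal costs, 30 per arm, 10,000 simulated trials per setting, control median 100 and log-SD 0.5. The true mean is median × exp(log-SD² ÷ 2), so for control 100 × exp(0.125) = 113.

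| Ultrasound median, log-SD | True mean, ultrasound v control | Rank test significantly favours ultrasound | Of those, ultrasound sample mean is higher |
|---|---|---|---|
| 60, 1.2 | 123 v 113 | 54% | 29% |
| 70, 1.2 | 144 v 113 | 30.5% | 36.5% |
| 70, 1.0 | 115 v 113 | 38% | 14.5% |
| 80, 0.5 | 91 v 113 | 37% | essentially none |

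Reversal needs a heavier upper tail in the arm with the lower median. With equal log-SD the two scales agree.

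**Step 3: the opposite direction.** Suppose the strategy raises surfactant use from 40% to 70% and cuts long stays from 20% to 15%. Base cost is log-normal with median 6 (log-SD 0.25), surfactant costs c, and a long stay adds 15. The expected mean difference is (0.70 − 0.40)c + (0.15 − 0.20) × 15 = 0.30c − 0.75, which is −0.45 for c = 1 and −0.15 for c = 2. By simulation the median rises by 0.15 and 0.43, and the chance that an ultrasound infant costs more than a control infant is 0.515 and 0.545. The mean falls while the median and ranks point to higher cost.

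**Step 4: the same inputs at 30 per arm.** The rank statistic and the sample mean difference had opposite signs in 24% (c = 1) and 29% (c = 2) of simulated trials. A significant rank test for higher cost with ultrasound was uncommon: 3.2% and 8.0%, against 2.5% by chance. The sample mean difference itself had the wrong sign in 39% and 46%, with a 95% interval half-width of about 3.0 units.

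**The case against.** The case for leaving the text alone has four parts.

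- *Cost is incidental.* It is missing from the outcomes in 2.9, from the abstract's hypothesis and from the Conclusion, and the Background sentence is hedged. This stands. A reader might infer that the trial promises to lower cost or has an economic endpoint; the documents support neither. It limits the weight of the point, but cost is still collected as an assessed outcome and named as a possible benefit.
- *Section 2.13 never mentions cost, and a fuller plan may treat it separately.* Partly fair, since a condensed article need not give a method for each variable. But the rule is stated for continuous data without exception, and as written it covers cost. The objection is to a stated rule, not to silence.
- *The reversal is invented.* This stands for its size and direction. A reader might infer that the rank test will show higher cost here while spending falls. That requires more surfactant use, whereas the Background cites retrospective work in which ultrasound scoring lowered use by 30.1%; lower use removes the mechanism in step 3. Step 2 needs a heavier tail in the ultrasound arm, which the documents do not suggest either.
- *The remedy is imprecise at this size.* This also stands, as step 4 shows. A mean difference from 60 infants may well have the wrong sign. Its advantage is that it addresses the right quantity and shows its uncertainty, which a median contrast with a P-value does not.

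**Conclusion.** The point holds as a minor, inexpensive improvement. If cost is skewed, the 2.13 rule yields no estimate of the change in mean or total expense, and this does not depend on any reversal. If cost is judged normal, the *t*-test compares means and the point falls away.

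That ranks and means can point in opposite directions is established, but only for arms whose cost distributions differ in shape. How likely or how large this would be in this trial cannot be derived from the documents. Under the step 3 assumptions, the likelier harm is a misleading median contrast rather than a significant result in the wrong direction. The conclusion assumes that medical expenses are meant as money spent overall, which the documents do not spell out. The primary outcome, the secondary outcomes in 2.9 and the sample size are unaffected.

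**What to change.** Add one sentence to 2.13 that exempts cost from the normality rule: report the arithmetic mean cost per infant in each arm and the difference in means with a bootstrap 95% confidence interval, with the median and quartiles as description only. Resample whole sibling sets, each infant keeping its own arm, because 2.3 randomises multiples individually and siblings' costs may be correlated. Label the comparison exploratory.

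The cost is that sentence and a short program. No further data and no change in sample size are needed. The drawback is a wide interval with 60 infants, which may leave the direction of the cost difference undecided.

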## Discussion

3

In recent years, there has been an increasing focus on using LUS to predict the need for PS administration. De Martino et al. indicated the potential of LUS for predicting PS administration (11). Rodriguez-Fanjul et al. enrolled 56 very preterm infants, with a GA of less than 32 weeks, and divided them into a lung ultrasound and control group. In the lung ultrasound group, PS administration was guided by LUS or FiO_2_ levels within 1 h after birth, while in the control group, it was based on the FiO_2_ level alone. Ultimately, they discovered that the lung ultrasound group exhibited better oxygenation statuses and lower FiO_2_ requirements post-PS administration (23). Raimondi et al. categorized preterm infants with a GA of less than 34 weeks by age and conducted weekly lung ultrasonography and scoring from birth. They concluded that LUS showed a significant correlation with oxygenation status and could partly predict the occurrence of late-stage BPD (24). At present, there are also ongoing multi-center randomized controlled clinical trials (25).

Regarding the selection of the time point for the first pulmonary ultrasound after birth, previous studies have mostly set the time point between immediately and 3 h after birth (11, 26). As early as 2009, the “golden hour” management concept was introduced into the early treatment of premature infants and is believed to have improved the long-term prognosis (17, 18). In this study, the selection of the first pulmonary ultrasound examination at 1 h after birth was also based on this concept. Our NICU ward is relatively close to the delivery room, and only patients born in our hospital without severe asphyxia are selected as the study objects. Some of these patients can be transferred to the NICU ward within 15 min after birth and do reach a stable state within a short time after birth (owing to factors such as positioning of the vascular access, stabilization of ventilatory parameters, and thermal homeostasis) (18). Therefore, the subjects had received stable respiratory support for a long enough time at 1 h after birth for a pulmonary ultrasound assessment to be appropriate. The selection of LUS >8 as the cut-off value of PS in this study is also based on the results of previous studies (11, 23, 25, 27).

Although there are many clinical studies attempting to use LUS to evaluate the administration of PS, it has been suggested that LUS may fail to precisely evaluate the severity of lung lesions in patients (28). Moreover, conditions other than NRDS can also lead to elevated LUS, such as severe pulmonary edema, meconium aspiration syndrome, and pneumonia. Relying solely on LUS for determining the administration of PS is considered inadequate.

Based on prior research, this study protocol has been refined and improved in the following aspects: (1) Patient selection: very preterm infants with a GA of less than 32 weeks will be selected. According to previous study reports, the incidence of NRDS increases gradually with a decrease in GA. The incidence of NRDS in extremely preterm infants (GA ≤28 w) has been reported to be 93%; however, even among late preterm infants at 34 weeks GA, 10.5% of patients were diagnosed with NRDS (29, 30). In preterm infants below 32 weeks GA, early postnatal respiratory distress can be caused by a variety of causes. Differential diagnosis through traditional imaging is not only less sensitive but also brings about the challenges of radiation exposure. Patients often have delayed application or overuse of PS owing to misdiagnosis. Our study will include this population as the research object, hoping to identify NRDS more accurately and guide PS application through non-invasive methods in the early stage. (2) The clinical application of LUS was optimized: most previous studies judge whether to use PS only according to LUS, ignoring the possibility that other diseases causing respiratory distress may be misdiagnosed as NRDS. The severity of lung lesions caused by different diseases cannot be compared in parallel by LUS. In our study, the researchers first diagnosed NRDS through lung ultrasound and then assessed the severity of NRDS according to LUS and guided the application of PS. The combination of qualitative diagnosis and semi-quantitative assessment was more reasonable. In the diagnosis of NRDS by pulmonary ultrasound, the lesions may appear in any lung field; the pulmonary ultrasound guidelines clearly indicate that the lung lesions of NRDS mainly appear posteriorly, and therefore, the examination of the posterior region should not be ignored (19). In previous studies, in order to avoid moving patients, only the anterior and lateral lung fields were examined and scored, which may affect the accuracy of results (25, 31). In our study, according to the pulmonary ultrasound guidelines for lung partitioning, the anterior, lateral and posterior lungs were comprehensively evaluated and the scores of each lung field were recorded; the final total score was then calculated, which will be more accurate than the calculations in previous studies. (3) Timing of lung ultrasonography: previous studies have limited time points for lung ultrasound assessments, usually within the first 24 h post-birth. However, in the early postnatal period, premature infants experience rapid changes in their conditions and may require repeated administration of PS. Therefore, in our study design, the ultrasound group will undergo multiple lung ultrasound examinations within the first hour after birth, 4–10 h after the initial PS administration, prior to subsequent PS administration, and at 24- and 72-h post-birth. This will be the highest frequency of lung ultrasound examinations among known studies of the same type, and this approach allows for better monitoring of early postnatal lung ultrasound dynamics. Additionally, follow-up lung ultrasonography will be conducted at 1, 2, and 4 weeks after birth, as well as before discharge, thereby providing a basis for prognostic assessment; (4) Treatment method: following the 2022 European Consensus Guidelines on the Management of Respiratory Distress Syndrome, NCPAP combined with LISA was identified as the preferred treatment for preterm infants with spontaneous breathing after birth (2). Therefore, in this study, for infants receiving non-invasive ventilation (NCPAP or NIPPV) and exhibiting spontaneous breathing, priority will be given to the LISA method to reduce the risk of airway injury. This study aims to combine non-invasive diagnosis methods with non-invasive treatment to reduce the requirement for early invasive operations after the birth of preterm infants.

This study has several potential limitations: (1) Blinding ultrasound physicians and neonatologists to the grouping situation is impractical because the decision on PS administration relies on lung ultrasound results post-patient enrollment. However, subsequent ultrasound results, except for the first one, will not be disclosed to the clinicians to avoid influencing decisions on subsequent treatment. (2) Premature infants with respiratory distress will not be immediately grouped after birth but will instead be grouped upon arrival at the NICU. Nevertheless, it is stipulated that the same T-piece resuscitator should be used for non-invasive respiratory support during resuscitation in the delivery room and transportation process, and the infants should arrive at the NICU within 15 min after birth. (3) This study has a small sample size and is conducted at a single center. Future research will need to expand the study scope and increase the sample size.

## Conclusion

4

If the study hypotheses are confirmed, it may establish a foundation for early PS administration in very premature infants based on NRDS diagnosis and LUS in the early postnatal period. This approach aims to optimize PS utilization, minimize x-ray exposure, reduce mechanical ventilation duration, lower BPD incidence, and ultimately enhance patient prognosis.
